### Data collection and management

Data will be collected with electronic questionnaires which can be completed via the website of LimeSurvey (www.limesurvey.org). LimeSurvey is approved by the Amsterdam UMC to collect data and LimeSurvey never discloses data publicly, nor transfers any data to any third party without consent. In LimeSurvey data is stored in a separate database with a separate username and password for each LimeSurvey Cloud instance. The data will be collected at four different time points: during screening (T0), 4 weeks after screening (T1), 9 weeks after screening (T2), and 22 weeks after screening (T3). Data of the participants will be stored in a secured map on the local network of the Amsterdam UMC. The secured map is only accessible to the researchers of the Amsterdam UMC and to the members of the Clinical Monitoring Center of the Amsterdam UMC who will monitor this study. If data is transferred electronically from the researchers to the PGAP coaches, it will be sent through a secured file sender. Only project group members will have access to all the data collected. PGAP coaches have only access to the scores on the questionnaires of the participants they coach.

### Statistical analyses

Statistical analyses will be conducted in SPSS statistics 26. All analyses will be described in a statistical analysis plan, which can be provided upon request. All analyses will be performed according to the intention-to-treat principle. Descriptive statistics will be used to describe the control and intervention groups.

Generalized Linear Mixed Models will be used to study the effects of PGAP on the primary outcome catastrophizing as measured with the SCS at Times T1, T2, and T3, using baseline catastrophizing as a covariate.

Generalized Linear Mixed Models will be used to study the effects of PGAP on the following secondary outcomes, which are all continuous variables at Times T1, T2, and T3: score RTW self-efficacy scale, score QWLQ, score on WAI, score RTW Expectations, score RRTW scale, score on motivation scale, score TSK, score IEQ, score GPDI, score PHQ-9, score MFI, score SF-12, the mean number of working hours, and the mean number of working days. In the analyses, we will adjust for the baseline scores on these measures.

Mixed effects logistic regression will be used to study the effects of PGAP (intervention or control) on the secondary outcome work status (binary variable: back to work or on sick leave) at T1, T2, and T3.

To examine whether decreases in catastrophizing or fear-avoidance beliefs or increases in RTW self-efficacy, motivation, or RTW expectations serve as mediators for the effects of PGAP on changes in working hours we will use the approach of Baron and Kenny (Fig. 2) [45]. We will analyze whether PGAP influences working hours (c), potential mediators (a), and whether the potential mediators influence working hours (b). Finally, we will analyze whether the magnitude of the effect of PGAP on working hours reduces in magnitude when we include the mediators in the model (c’).

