Workability will be measured using the Dutch version of the Work Ability Score and two additional questions of the reliable and valid Work Ability Index (WAI) [36–38]. The Work Ability Score is the worker’s self-assessment of his/her current ability ranging van 0 to 10. In the other two questions of the Work Ability Index, the workers rate his/her workability in relation to the physical and mental work demands. The questions can be answered on a five-point scale from “very poor” to “very good.”

RTW expectations will be measured using the questions: “What are your chances of being fully able to work one month from now?” and “What are your chances of being fully able to work three months from now?” The questions can be answered on a scale from 0 to 100%.

Readiness for RTW will be measured with the Dutch Readiness for RTW scale (RRTW) [39, 40]. This questionnaire has 21 items with a five-point scale from “strongly disagree” to “strongly agree.” Twelve of these items are only completed by participants who did not RTW and 9 items are only completed by participants who returned to work. The scores of this questionnaire indicate in which stage the worker is when it comes to returning to work: pre-contemplation, contemplation, preparation for action-self-evaluative, preparation for action-behavior, uncertain maintenance, and proactive maintenance. The Cronbach’s alpha for these dimensions varied from .65 to .82 in previous studies [39].

Motivation will be asked with one statement that can be answered on a five-point scale from “totally disagree” to “totally agree.” The statement for participants who returned to work is “I am motivated to stay at work.” The statement for participants who did not RTW is “I am motivated to RTW”.

Depressive symptoms will be measured with the Dutch version of the Brief Patient Health Questionnaire-9 (PHQ-9) [41]. The questionnaire contains 9 items which can be answered on a four-point scale from “not at all” to “nearly every day”. In addition, there is a tenth item in which the participant can indicate how difficult the problems of the participant have been lately. The final score can range from 0 to 27 in which a higher score indicates more severe depressive symptoms. The Cronbach’s alpha for the PHQ-9 varied from .86 to .89 in previous studies and was proven to be a valid questionnaire for measuring depressive symptoms [41].

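### Readiness for return to work (RRTW) is fixed as one continuous, baseline-adjusted score, although returned and non-returned workers answer disjoint item sets that yield a stage

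*Protocol article*

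**What the plan says.** In the protocol article, Statistical analyses, fourteen measures are to be analysed with generalized linear mixed models as "secondary outcomes, which are all continuous variables at Times T1, T2, and T3". The list includes "score RTW Expectations, score RRTW scale, score on motivation scale, score TSK", and each measure is adjusted for its own baseline score. The same section names motivation as one of five candidate mediators of the effect on working hours.

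The Secondary outcomes section describes the two measures as follows.

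- **RRTW:** 21 items, of which "Twelve of these items are only completed by participants who did not RTW and 9 items are only completed by participants who returned to work". On the output it says: "The scores of this questionnaire indicate in which stage the worker is when it comes to returning to work". Six stages are named, and reliability is reported per dimension. No total or mean score is defined.
- **Motivation:** "Motivation will be asked with one statement that can be answered on a five-point scale". Its target depends on work status: remaining in work for those who have returned, going back to work for those who have not.

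The hypotheses at the end of the Background expect a greater chance of return to work with PGAP.

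**The concern.** A continuous outcome in a mixed model needs one quantity that means the same for every participant at every visit. The RRTW, as described, does not supply one. The set of items answered is decided by work status at the visit. That status arises after randomisation, and the trial expects it to differ between the arms.

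Two readings of the planned analysis are open, and neither gives a clean randomised comparison.

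- If scores from both item sets are pooled, part of the arm difference reflects which set was answered rather than readiness.
- If scores are compared within returned or within non-returned workers, the analysis conditions on a consequence of treatment and leaves the intention-to-treat comparison that the section promises.

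The baseline covariate does not help. A worker on leave at T0 who later returns has a baseline value and a follow-up value built from different items.

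**Working it through.** **1. The plan's own figure.** The article gives no figure for RRTW or motivation. Its only calculation is the sample size for the primary outcome, and it reproduces: 2 × (1.960 + 0.842)² × (3.0 / 2.4)² = 24.5, so 25 per group; 25 / 0.85 = 29.4, so 30 per group and 60 in total. (This takes .05 as two-sided and .80 as power.) Nothing below changes it.

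**2. Item overlap.** 12 + 9 = 21, which is the full questionnaire, so the two sets share 0 items. For a worker whose status changes between T0 and follow-up, the covariate and the outcome have 0 of 21 items in common.

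**3. Is a single score defined elsewhere?** For most other multi-item scales (SCS, TSK, IEQ, GPDI, RTW-SE, QWLQ, PHQ-9, MFI, SF-12) the article gives a range or a scoring rule for one score. For the RRTW it gives stages only.

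**4. What pooling does.** Let pI and pC be the shares returned to work in the PGAP and control arms, and g the mean on the returned form minus the mean on the non-returned form. With no PGAP effect within either status group, the arm difference is

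D = (pI − pC) × g.

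The article gives neither the shares nor g. The following values are assumptions, chosen only to show the range: pC = 30%, pI = 50% to 70%, so pI − pC = 0.2 to 0.4.

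*RRTW, if it were summed with items coded 1 to 5.* The possible ranges are 12–60 (not returned) and 9–45 (returned). With the same item mean m on both forms, g = 9m − 12m = −3m.

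| pI − pC | m = 3 (g = −9) | m = 4 (g = −12) |
|---|---|---|
| 0.2 | −1.8 | −2.4 |
| 0.3 | −2.7 | −3.6 |
| 0.4 | −3.6 | −4.8 |

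The arm with more returned workers would score lower from item count alone. Using an item mean removes the count effect but still compares different items.

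*Motivation, five-point item.* With g = 0.5: 0.2 × 0.5 = 0.10 and 0.4 × 0.5 = 0.20. With g = 1: 0.20 and 0.40. The sign follows the sign of g, which is unknown.

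If pI = pC, D = 0. The article hypothesises that the shares differ.

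**5. Room for an ordinal analysis.** Sixty participants over six stages average 60 / 6 = 10 per stage across both arms, and the 50 needed for the power target average 50 / 6 = 8.3. Some stages will probably be sparser than that.

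**The case against.** The strongest reply is that the score may simply mean the stage coded 1 to 6. Instrument scoring is normally left to the SAP, which the article says exists and which is not shown. The summed score in the illustration is planned nowhere in the article. All this is fair, and it means a common metric is available, namely the stage. But a stage is an ordered category, not a continuous variable, and the article states the latter for every outcome on the list. An SAP that treated it properly would depart from the article, so the text needs correcting either way.

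Other points that stand:

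- RRTW and motivation are two of fourteen listed secondary outcomes, motivation is one of five mediators, and neither is named in the hypotheses. A reader might infer that the trial's main conclusion is at risk; the article does not support that.
- A reader might take the illustrative differences as estimates of bias. They rest on assumed return rates and form gaps, and the effect vanishes if return rates are equal.
- A reader might put motivation on the same footing as RRTW. It keeps one statement on one response scale, and wording fitted to work status is a defensible choice. Treating a five-point item as continuous is common. Only the change of target matters.
- An ordinal stage analysis is not a complete cure. The two maintenance stages appear, from their names, to apply only to returned workers, so the outcome partly repeats work status, which is analysed separately. T0 and follow-up stages may still come from different item sets. Categories may be sparse.

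**Conclusion.** The RRTW analysis is wrong as written: the article fixes a single continuous score for an instrument that it describes as two disjoint item sets leading to a stage. Since the set answered depends on a post-randomisation outcome that PGAP is meant to change, a pooled score compares unlike quantities between arms and over time. This rests on the article's text alone, together with its own hypothesis on return to work. The size is not estimable from the article.

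For motivation, the arm contrast and the mediator analysis are partly confounded with work status. That is a minor point, of unknown size and direction.

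This should be fixed, as a matter of secondary outcomes only.

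**What to change.** **RRTW**

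- Take it off the continuous list.
- Analyse the allocated stage at T1, T2 and T3 in all randomised participants as one ordered outcome (for example a cumulative-logit mixed model), with T0 stage as covariate and no split by work status.
- Prespecify how sparse stages are collapsed. If the model cannot be estimated, report the stage distribution by arm descriptively.
- State that the maintenance stages appear open only to returned workers, so the result partly reflects return to work.
- Keep item-level or dimension scores within a work-status group descriptive.

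**Motivation (minor)**

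- Either put one identically worded statement to everyone from T0 to T3,
- or report the two versions descriptively and drop motivation as a mediator.

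**Cost.** The RRTW change is a few lines in the analysis section and the SAP; the price is a less familiar summary with limited information at 30 per arm. Rewording the motivation item is an amendment that needs ethics committee approval (Data monitoring). The protocol version is dated April 2022 and recruitment is planned from September 2022 (Trial status), so the change is best made before the first T0 questionnaire. The descriptive option needs no new item.

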### Sample size

Results of power analysis (*α* = .80, *p* < .05) show that at least 25 participants per group are needed to detect a change in post score of 2.4 points on the primary outcome catastrophizing as measured with the Symptom Catastrophizing Scale (SCS; SD = 3.0). The standard deviation of 3.0 points and the change of 2.4 points on the SCS are based on a previous study on the effects of PGAP by Moore et al. [23]. On the basis of previous research on the effect of PGAP, we expect that we will lose 15% of the participants in follow-up [24]. Therefore we aim to randomize at least 60 participants; 30 in the control group and 30 in the intervention group.

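### The Baron and Kenny steps chosen for the mediation analysis depend on a total effect the trial is not sized to detect, give no interval for the indirect effect, and set no time order between mediator and working hours

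*Protocol article*

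**What the plan says.** The last paragraph on methods under Statistical analyses names catastrophizing, fear-avoidance beliefs, return-to-work (RTW) self-efficacy, motivation and RTW expectations, and asks whether they "serve as mediators for the effects of PGAP on changes in working hours we will use the approach of Baron and Kenny". The steps are the effect of PGAP on working hours (c), its effect on each mediator (a), and the effect of the mediator on working hours (b). The closing step asks "whether the magnitude of the effect of PGAP on working hours reduces in magnitude when we include the mediators in the model" (c'). No test or interval for the indirect effect is named, and no visit is assigned to mediator or outcome.

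Under Data collection and management, the follow-up assessments fall "4 weeks after screening (T1), 9 weeks after screening (T2), and 22 weeks after screening (T3"). The mediators and working hours are listed for analysis at all three.

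Under Sample size, the calculation concerns the SCS only: "at least 25 participants per group are needed to detect a change in post score of 2.4 points". With 15% expected loss, "we aim to randomize at least 60 participants; 30 in the control group and 30 in the intervention group". No calculation is given for working hours or for mediation.

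**The concern.** The method is fixed in the article itself, so this is a stated choice and not a detail left to the statistical analysis plan. It has three weaknesses.

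- **The total effect acts as a gate.** In its usual form the approach goes on to mediation only if c is significant. When the effect runs through the mediator, c is about a×b, which is smaller than a and often harder to detect than either path.
- **The final criterion carries no uncertainty.** A c' smaller than c can arise by chance, and the comparison does not say how large the indirect effect is or how well it is known.
- **No time order is set.** Working more hours could plausibly raise RTW expectations and self-efficacy. Two features of the trial make this more than theoretical. PGAP can end at return to work (Intervention). The motivation item is worded differently for those who have and have not returned (Secondary outcomes).

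At stake is what the trial can say about how PGAP works: a false report of no mediation, or a report of mediation that in fact runs from hours to cognition.

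**Working it through.** **1. The plan's own figure.** Inputs from Sample size: difference 2.4, SD 3.0, so d = 2.4/3.0 = 0.8; power 0.80; significance level 0.05, taken as two-sided. Normal approximation: n = 2(1.96 + 0.84)²/0.8² = 24.5, so 25 per group, as stated. Dropout: 25/0.85 = 29.4, so 30 per group and 60 in all, as stated. Expected number at follow-up: 60 × 0.85 = 51.

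**2. Power for the total effect on hours at 51** (two-sample t-test): 18% for 0.3 SD, 42% for 0.5 SD and 80% for 0.8 SD. Under full mediation with a = 0.8 and b = 0.5, c = 0.8 × 0.5 = 0.40 SD. Simulated power is then 29% for c, against 78% for a and 96% for b. The c step is the bottleneck.

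**3. Simulation of the steps.** Model: M = aX + e₁ and Y = bM + c'X + e₂, with N = 51, 1:1 allocation, ordinary least squares and 3000 runs per scenario. The steps succeed if c, a and b are each significant at two-sided 0.05 and |c'| < |c|. The comparator is a simulated (Monte Carlo) 95% interval for a×b that excludes zero. The document gives no path sizes, so all are assumed; a = 0.8 borrows the planning effect for the SCS.

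| a | b | c' | Steps | Interval on a×b |
|---|---|---|---|---|
| 0.5 | 0.3 | 0 | 2.8% | 23% |
| 0.5 | 0.5 | 0 | 9.9% | 42% |
| 0.8 | 0.3 | 0 | 6.2% | 46% |
| 0.8 | 0.5 | 0 | 25.9% | 77% |
| 0.5 | 0.3 | 0.3 | 10.6% | 24% |
| 0.5 | 0.5 | 0.3 | 28.1% | 43% |
| 0.8 | 0.3 | 0.3 | 22.6% | 46% |
| 0.8 | 0.5 | 0.3 | 59.2% | 79% |

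With a = 0.8, b = 0.4 and c' = 0 the figures are 15% and 68%. The table takes residual variance 1 − b² for hours; a residual SD of 1 gives somewhat lower values. Over both scalings, with a = 0.8 and b = 0.4 to 0.5, the steps reach 12-26% under full mediation and 34-59% with c' = 0.3, against about 62-80% for the interval. The steps would need about 200 participants for 80% power with a = 0.8, b = 0.5, c' = 0, and about 600 with b = 0.3.

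**4. Effect of baseline adjustment.** With an assumed baseline correlation of 0.5-0.7, a = 0.8 and c' = 0.3, the steps reach 52-66% (b = 0.4) and 70-88% (b = 0.5). With c' = 0 they stay at 19-47%.

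**5. False mediation at N = 51.**
- No mediator effect (b = 0), a shared cause carrying 30% of the variance, and a direct effect of 0.5 SD: the steps declare mediation in 21% of trials. Joint significance of a and b does so in 45%.
- Hours drive the supposed mediator at the same visit (effect on hours 0.5-0.8 SD, correlation 0.5-0.7): the steps declare mediation in 9-47%.

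**The case against.** Several points on the other side stand.

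- **The gate is not in the protocol's words.** The text says the effect on hours will be analysed; it does not say that mediation is abandoned if c is not significant. The gate is the conventional reading of the named method, and every percentage for the steps depends on it.
- **The path sizes are assumed.** The 0.8 SD belongs to the SCS, one of five mediators. PGAP also includes activity planning and problem-solving, so a direct effect is plausible and full mediation is a hard case for the steps. Baseline-adjusted repeated measures, planned for these variables elsewhere, would raise power.
- **An interval on a×b is not a cure by itself.** Under a shared cause, testing the two paths gives more false mediation than the steps (45% against 21%).
- **Mediation is ancillary.** It appears in neither the two objectives nor the hypotheses in the Background.

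A reader might also infer, because mediators and hours are collected at the same visits, that the plan pairs same-visit values and so cannot tell mediator from consequence. The document does not support that. The paragraph pairs no visits at all, T1 to T3 allow a lagged analysis, the figure showing the mediation model is not available, and the statistical analysis plan may supply the order.

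What the objections leave untouched is the choice of method: in every true-mediation scenario tabulated above, the interval on a×b found mediation more often than the steps.

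**Conclusion.** The concern holds in limited form. The article commits to a method that, as conventionally applied, passes through a test the trial is not sized for and ends in a comparison without an interval. At about 51 participants the loss is large under full mediation (roughly 12-26% against 62-80%, with a = 0.8 and b = 0.4 to 0.5). It is smaller with a direct effect of 0.3 SD (34-59%), and smaller again with baseline adjustment. The direction is firm; the size rests on assumed paths, one time point, no baseline adjustment and the conventional gate on c. A flat statement that the plan will usually miss mediation would therefore go too far: with baseline adjustment, a direct effect and strong paths, the steps exceed 50%.

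On time order, the supported statement is that the paragraph, as written, does not ensure that the mediator precedes the outcome. No conclusion about the effectiveness of PGAP depends on this analysis. It merits correction because the change is cheap and the result would be read as evidence on mechanism.

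**What to change.** Replace the steps with the following:

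- Estimate the indirect effect a×b for each mediator with a percentile-bootstrap 95% CI, and do not require c to be significant.
- Take the mediator at an earlier visit than working hours, for example T1 or T2 for the mediator and T3 for hours, and fix the choice in advance.
- Adjust both the mediator model and the hours model for the T0 mediator and T0 hours.
- Label the analysis exploratory.

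State two limits alongside it. Power for a×b remains about 20-46% if either path is modest, so an interval that includes zero would not show absence of mediation. The lag and baseline adjustment reduce confounding and reverse causation but do not remove them: causes arising after baseline stay unadjusted, and some participants may already be working by T2.

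The cost is a change of wording. The measures are already scheduled and, with recruitment due to start in September 2022 (Trial status), not yet collected. The downside is that only one lag is used.

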**Fig. 2 Fig2:**
[figure not shown]
Model mediators following the approach of Baron and Kenny [45]

Because the participant completes all questionnaires online and it is not possible to skip items, we do not expect missing items. However, it is possible that participants drop out and do not complete all questionnaires because of the longitudinal design of this study. We took this into account in our power analysis. Besides, the intention-to-treat analysis will be conducted to evaluate whether there are differences between the participants that completed all questionnaires and the participants who dropped out.

### Data monitoring

The Clinical Monitoring Center of the Amsterdam UMC will be responsible for monitoring. The monitors are in no other way involved in this study and there is no conflict of interest. Monitoring visits will take place during the study and are carried out on the basis of a monitoring plan. After each monitor visit, the monitor writes a report in which the findings are mentioned. Further details about its charter can be provided upon request.

Because no risks are associated with participation in this study, no interim analyses are conducted and no stopping guidelines are formulated. Although no (serious) adverse events are expected, adverse events will be reported to the sponsor, which will report them to the Medical Ethics Review Committee. No auditing is planned. Amendments to the research protocol will be reported to the Medical Ethics Review Committee for approval.

